### Randomization and blinding

Participants are randomized using a Good Clinical Practice-compliant system (CastorEDC; https://www.castoredc.com/), which employs stratified, variable block randomization. After their baseline visit, participants are randomized in a 1:1 ratio to the treatment (MBCT + CAU) or control (CAU) group. The randomization sequence is determined by variable block sizes (2,4) and is stratified by gender (female, male, or other) and age (< 65 years old, and ≥ 65 years old). Group allocation is communicated by the coordinating researcher (FG) after T0. Participants are aware of the study design and are therefore not blinded to their study condition. Data acquisition will be performed by the coordinating researcher, hence data acquisition is not blinded. Outcome measures involving structural and functional neuroimaging, as well as other biological markers or self-report questionnaires are unlikely to be influenced by the (unblinded) researcher. To enable post-hoc ratings of disease severity (score on MDS Unified Parkinson’s Disease Rating Scale (UPDRS) III) by an independent and blinded researcher, motor performance will be video-recorded.

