### Power and sample size estimate

The primary outcome is the HADS-total score at T1 (post-intervention). Based on a recent large RCT analyzing the effects of an MBI on the HADS in people with PD [13], we expect a moderate effect size (*d* = 0.48). This is also in accordance with a recent review of 44 meta-analyses investigating the effects of MBIs in different clinical populations, reporting effect sizes between 0.45 and 0.75 after an MBI when compared to care as usual [10]. Considering an effect size of 0.48, a comparison of two groups of 70 subjects would yield 80% power with a two-sided alpha of 0.05. We corrected our power for correlations between the covariate (HADS at T0) and outcome measure (HADS at T1), given our planned statistical model where we will include HADS at T0 as a covariate (see below). Assuming a conservative correlation (r) of 0.5 between these two measures, a sample size of *n* = 53 [70 × (1-r^2^)] patients per group is required [45]. Considering a potential drop-out of 15%, we will include 62 individuals per group. This sample size allows us to detect an absolute difference in HADS score of 3.1, which exceeds the minimal clinically important difference for the HADS in people with PD [24]. This will also allow us to demonstrate group effects with an effect size of > 0.50 for our secondary outcomes [46, 47].

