#### Primary outcome

To determine whether MBCT can reduce symptoms of anxiety and depression in people with PD, our *primary analysis* will test the effects of GROUP (MBCT vs. CAU) on the HADS-total after treatment (T1). Specifically, an analysis of covariance (ANCOVA) will be used with HADS score at T1 as dependent variable and GROUP as fixed factor. Age at T0, gender and HADS at T0 will serve as covariates. *Secondary analyses* will explore the consolidation of treatment effects across TIME (T0 vs. T1 vs. T2) using mixed models (fixed effects: time, group, time*group; random intercept for SUBJECT). In case of a significant intraclass correlation coefficient, we will add COHORT as a random effect to account for clustering within intervention cohorts. Potential moderators of the treatment effect, such as cognitive impairment (MoCA at T0), disease severity (defined as time since diagnosis made by a neurologist), or age may be explored to identify subgroups of patients that particularly benefit from the intervention. Also, mediators of the effect, such as mindfulness skills (FFMQ), self-compassion (SCS), or rumination (RRS) may be tested, to explore psychological mechanisms underlying the effect of MBCT on symptoms of anxiety and depression.

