#### Clinical assessments

To explore whether MBCT has an effect on motor symptom severity, we will test the effect of TIME (T0 vs. T1 vs. T2) and GROUP (MBCT vs. CAU) on MDS-UPDRS III scores in a linear mixed model (LMM) for repeated measures. We will also explore tremor amplitude as a function of GROUP (MBCT vs. CAU), TIME (T0 vs. T1 vs. T2) and CONDITION (rest vs. cognitive coactivation) using LMM. Similarly, bradykinesia scores derived by the key tapping task will be investigated as a function of GROUP and TIME. Further explorative analyses will test the effects of GROUP and TIME on cognitive abilities (MoCA), as well as self-reported psychological wellbeing and mindfulness skills (perceived stress, rumination, self-compassion, self-efficacy, positive appraisal style, mindfulness skills, social support and quality of life).

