#### Laboratory measurements

To explore whether MBCT influences biochemical markers of stress, the area under the curve with respect to increase [48] of *salivary cortisol* secretion pre- until 60 min post stress induction will be assessed as a function of TIME (T0 vs. T2) and GROUP (MBCT vs. CAU), while considering relevant covariates, such as age and gender. The predictive value of e.g. HADS at T0 and disease duration on the cortisol response will be explored using LMM. Similarly, changes in *hair cortisol levels* will be compared between T0, T1 and T2, and GROUP by means of LMM. To test the effect of MBCT on inflammatory tone (*hs-CRP*), causal mediation analysis techniques will be used to decompose causal effects of stress on neurodegeneration into four components: mediation (by inflammation) only, interaction (with inflammation) only, both, or neither.

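### The secondary HADS mixed model treats pre-randomisation T0 as an outcome with a free group difference, so it compares changes from baseline and gives up precision that the primary ANCOVA keeps

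*Protocol article*

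**What the plan says.** In the protocol article, under Statistical analyses, Primary outcome, the primary test is an ANCOVA of HADS at T1 on group, for which "Age at T0, gender and HADS at T0 will serve as covariates". The secondary analyses of the same scale take T0, T1 and T2 as the levels of time and are to be carried out "using mixed models (fixed effects: time, group, time*group; random intercept for SUBJECT". T0 is thus one of the outcome times, and group has its own main effect there.

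Under Statistical analyses, Clinical assessments, a similar layout appears for motor severity: "we will test the effect of TIME (T0 vs. T1 vs. T2) and GROUP (MBCT vs. CAU) on MDS-UPDRS III scores". The Behavioral assessments section crosses the same two factors for the controllability task. Neither section gives a full list of fixed effects.

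The Power and sample size estimate section reduces 70 per group to 53 by the factor 1−r² with r = 0.5 for HADS T0 with T1, and recruits 62 to allow for 15% dropout. It then adds: "This will also allow us to demonstrate group effects with an effect size of > 0.50 for our secondary outcomes". No power, correlation, number of completers or model accompanies that sentence.

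**The concern.** Randomisation follows the baseline visit, so the two arms have the same expected T0 mean. A model that still estimates a T0 group difference subtracts the observed baseline imbalance in full, instead of in proportion to how well T0 predicts the outcome. The precision that justified cutting the sample from 70 to 53 per group for the primary test is then partly or wholly lost in the secondary HADS analysis, including the 12-month result. The same would apply to other outcomes wherever the same model is used for them. The report would also carry two estimates of the HADS effect at T1, one adjusted for baseline and one based on change, which need not agree.

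**Working it through.** **Inputs from the protocol article** (Power and sample size estimate): d = 0.48, two-sided alpha 0.05, 80% power, r = 0.5 (HADS T0 with T1), 70 then 53 then 62 per group, 15% dropout. **Assumptions not in the article:** equal variance at all times and one common correlation r between any two times. No r is given for other outcomes, so a range is shown. Effects are in SD units.

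**1. The plan's own figures.** n = 2(1.960+0.842)²/0.48² gives 69 per group. With the t distribution, power is 79.9% at 69 and 80.5% at 70, so 70 stands. 70 × (1−0.5²) = 52.5, rounded to 53. 52.5/0.85 = 61.8, rounded to 62. The sample size is reproduced.

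**2. What the planned model estimates.** With complete data, the time-by-group coefficient at T1 is (mean T1 − mean T0) in the MBCT arm minus the same in the CAU arm. In 60 simulated trials (53 per arm, r = 0.5) it matched the difference in mean change to within 5×10⁻¹⁵. The average standard error was 0.193 with a free baseline and 0.167 with a common T0 mean. The squared ratio is 0.0279/0.0372, or about 0.75.

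**3. Efficiency.** The variance factor is 2(1−r) for the change contrast and 1−r² for the adjusted contrast. Their ratio is (1+r)/2. The detectable d at 80% power is 2.802 × √(2/n) × √(variance factor). With n = 53, 2.802 × √(2/53) = 0.544.

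| r | change | adjusted | ratio | d, change | d, adjusted |
|---|---|---|---|---|---|
| 0.3 | 1.40 | 0.91 | 0.65 | 0.644 | 0.519 |
| 0.5 | 1.00 | 0.75 | 0.75 | 0.544 | 0.471 |
| 0.6 | 0.80 | 0.64 | 0.80 | 0.487 | 0.435 |
| 0.7 | 0.60 | 0.51 | 0.85 | 0.422 | 0.389 |
| 0.8 | 0.40 | 0.36 | 0.90 | 0.344 | 0.327 |
| 0.9 | 0.20 | 0.19 | 0.95 | 0.243 | 0.237 |

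**4. The 0.50 statement.** At r = 0.5 and 53 per arm, power at d = 0.50 is 73.0% (change) against 84.4% (adjusted). The completers needed per arm are 63 against 48. The change contrast reaches d = 0.50 when 0.544 × √(2(1−r)) = 0.50, that is at r = 0.578. With all 62 per arm and r = 0.5, the detectable d is 0.503 (change) against 0.436 (adjusted).

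**5. Both follow-ups together.** Take r = 0.5, 53 per arm and a constant d = 0.50 at T1 and T2. The 2-df interaction test has noncentrality 0.25 × (2/1.5) × 53/2 = 8.8 and 76% power. After adjustment it is 0.25 × (2/1.0) × 53/2 = 13.25, with 91% power. The averaged post-baseline contrast has variance factor 0.75 and 84% power, against 0.50 and 95% after adjustment.

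**6. Age and gender.** In the simulation, age carried a tenth of the outcome variance. Adding both covariates to the planned model changed the estimate by at most 4×10⁻¹⁵ and left the standard error at 0.19297. With a common T0 mean, the standard error moved from 0.167 to 0.164.

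**7. Unequal variances.** As an illustration, let the T0 SD be 0.8 of the T1 SD with r = 0.5. The change variance is 1 + 0.64 − 2 × 0.5 × 0.8 = 0.84, and the detectable d with 53 per arm is 0.544 × √0.84 = 0.499. The adjusted variance stays at 0.75, a ratio of 0.89.

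**The case against.** The planned model is standard, its interaction contrast is unbiased under randomisation, and modelling T0 is natural for a question about trajectories. The analyses are exploratory, and the ANCOVA is clearly named as primary, so two T1 estimates leave no doubt about which one decides. All of this stands, and it limits the point to efficiency and alignment.

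The full list of fixed effects is given only for the HADS. For other outcomes the article sketches factors, and the detail may sit in a fuller plan. This also stands: for those outcomes the recommendation applies only where the same layout is used.

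A reader might infer that the trial cannot show d = 0.50 on its secondary outcomes. The article does not support that. It attaches no power, r, completer number or model to the figure, and its r = 0.5 concerns only the HADS and is called conservative. The figure is also almost exactly what an unadjusted comparison of 62 per arm gives (0.503), and pooling both follow-ups gives 84% power even under the planned model. If the entry rule (HADS total above 10) narrows the T0 variance, the change contrast improves further.

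A reader might also infer that leaving out age and gender, by which randomisation "is stratified by gender (female, male, or other) and age", creates the change-score contrast or weakens it. It does neither: covariates that do not vary over time leave that contrast untouched. Nor are they absent everywhere, since the salivary cortisol analysis is planned "while considering relevant covariates, such as age and gender".

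**Conclusion.** The point holds as a matter of efficiency in an explicitly stated model. The secondary HADS mixed model uses T0 less well than the primary ANCOVA does. Adjusting for T0 would cut the variance of the T1 and T2 contrasts by 25% at r = 0.5 and 15% at r = 0.7, and with equal variances it is never worse for r below 1. The gain shrinks as r rises, and also if T0 varies less than the later scores. The planned analysis remains valid, and the primary test and the sample size are unaffected. The statement on effects above 0.50 is under-specified, not shown to be wrong: with 53 completers per arm, 80% power and a single-time change contrast, it fails at r = 0.5 (about 0.54) and holds from r of about 0.58. These figures assume equal variances, a common correlation and complete data at the stated n.

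**What to change.** 1. For the secondary HADS analysis, model T1 and T2 only, with T0 as a covariate, or keep T0 as an outcome and constrain the arms to a common T0 mean. The covariate form is safer if the entry rule narrows the T0 variance, because a random-intercept model with T0 as an outcome assumes equal variance over time.
2. Do the same where the group-by-time layout is applied to other outcomes measured at T0, such as MDS-UPDRS III and the controllability parameter.
3. Age and gender may be added for consistency with the primary model. No material gain in precision should be claimed for this.
4. Restate the secondary-outcome effect size with its completers per arm, r, power and model. For example, at r = 0.5, 53 per arm and 80% power: about 0.47 for a baseline-adjusted contrast, or about 0.54 for a single-time change contrast.

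The cost is wording in the analysis plan. No new data, visits or participants are needed.

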### Interventions

#### MBCT

The 8-week curriculum of the group-based intervention is in line with the MBCT program described by Segal and colleagues [19]. For the purpose of this study, the content of the self-study materials was slightly adjusted to address PD-related issues and difficulties explicitly. For example, materials specifically discuss mindful living with physical restrictions associated with PD, and describe how to deal with lifestyle changes imposed by the disease. The intervention is provided to groups of 8–10 patients, which are a combination of both MIND-PD study participants as well as people with other somatic illnesses, who are referred to the training otherwise. The MBCT consists of eight weekly sessions of 2.5 h and one 4-hour silence day between the 6th and 7th session. The sessions include meditation exercises (body scan, sitting meditation, gentle movement exercises, three-minute breathing space, daily activities with attention), psychoeducation and group discussions. Psychoeducation includes information about cognitive techniques, like monitoring and scheduling of events, as well as identification of negative automatic thoughts. In addition, all participants are encouraged to perform daily practice assignments at home for about 30–45 min per day, mainly consisting of meditation exercises. Teachers of the MBCT fulfill the advanced criteria of the Association of Mindfulness Based Teachers in the Netherlands and are registered in the Dutch register for mindfulness trainers (https://www.mindfulnessregister.nl/). These criteria are in line with the UK Mindfulness-Based Teacher Trainer Network Good Practice Guidelines for teaching mindfulness-based courses [20]. During each MBCT course, two supervision meetings are held between the mindfulness teacher(s) and the intervention supervisor (AS). In addition, two MBCT courses per teacher will be video-recorded in order to assess teacher competence and protocol adherence using the Mindfulness-Based Interventions-Teachers Assessment Criteria [21]. To monitor adherence of the participants to the intervention, the Mindfulness Adherence Questionnaire [22] will be administered during MBCT sessions 2–8, as well as every 2 months after completion of the intervention. To further encourage mindfulness adherence in the course of the follow-up period, participants will receive bi-monthly newsletters providing updates about the trial, as well as motivational videos and materials discussing mindfulness and its potential benefits. The MBCT intervention is an add-on treatment; participants remain on their usual (dopaminergic) treatment during the intervention. While participating in the study, patients are asked to refrain from starting any new treatments apart from the study intervention, unless prescribed by their doctor. Health care use in the intervention group is monitored as part of the home questionnaires at T0, T1 and T2, as well as 6 months after T0 by means of the Treatment Inventory of Costs in Patients with psychiatric disorders (TIC-P, item 1–14) [23]. At the same timepoints, relevant lifestyle factors are monitored in the home questionnaires.

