#### Recruitment

Patients will be recruited via three sources:

Attending clinicians at the outpatient clinic of the Radboudumc are asked to preselect patients they see during consultation or during a multidisciplinary meeting. In addition, we will recruit patients treated by neurologists in surrounding hospitals (for example in Den Bosch, Arnhem and Tiel). Attending neurologists will give information about the study and initial inclusion criteria. Only patients that show interest will receive more information about the study.We will contact patients that gave permission to be approached for new scientific studies about PD during their participation in previous studies in our center.The online platform ParkinsonNEXT (https://www.parkinsonnext.nl*)* will be used, through which people with PD can easily sign up for research projects. The ParkinsonNEXT website contains a webpage with general information about our project, including background information and the possibility to register directly. In addition, we will send an open invitation to participate in our study via ParkinsonNEXT to all registered patients living close to Nijmegen.

If people are interested to participate, the researchers will provide them with information and will invite them to complete the online screening questionnaires to check their eligibility. If the patient is interested and eligible, they will receive the participant information letter. A week later, the researcher will call to provide more information and answer remaining questions if necessary. Afterwards, the patient can give verbal consent and the first visit is planned. During the first visit, the procedure, details of the study and obligations of the participant and the clinical research team will be clearly explained to all patients once more, and written informed consent is obtained. Only subjects who can give legal consent will be included. Participants will be recruited in multiple study cohorts of 10–16 patients each. Accordingly, groups of ~ 5–8 patients will simultaneously participate in each study arm (exact numbers depend on the randomization algorithm).

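### The primary ANCOVA has no term for MBCT therapy groups, and the only clustering rule is gated on a weak ICC test and uses a cohort term that does not address MBCT-only clustering

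*Protocol article*

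**What the plan says.** Under Statistical analyses, Primary outcome, the protocol article states that "an analysis of covariance (ANCOVA) will be used with HADS score at T1 as dependent variable and GROUP as fixed factor". Age, gender and baseline HADS are the covariates. No cluster term is named. A secondary mixed model over T0, T1 and T2 follows, with a random intercept for subject. Directly after it comes the only sentence on clustering: "In case of a significant intraclass correlation coefficient, we will add COHORT as a random effect to account for clustering within intervention cohorts".

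The design is described elsewhere:

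- **MBCT:** "The intervention is provided to groups of 8–10 patients". These groups mix trial participants with people who have other somatic illnesses.
- **CAU:** no add-on intervention, so no treatment group.
- **Recruitment:** cohorts of 10–16 patients, such that "groups of ~ 5–8 patients will simultaneously participate in each study arm".
- **Baseline and follow-up assessment; Post-treatment assessment:** baseline is timed against the start of an intervention cohort, and both arms are assessed once that cohort's MBCT training has ended. A cohort is thus most naturally a two-arm wave.

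The sample size section makes no allowance for clustering.

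**The concern.** Patients in one MBCT course share a teacher, sessions and peers, so their HADS scores at T1 may be correlated. CAU patients share no treatment. The design is therefore partially nested: any therapy-group variance adds to the variance of the MBCT mean, and an ANCOVA that treats patients as independent omits it.

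The stated rule may not repair this, for three reasons. It may not reach the primary analysis at all. It depends on a significance test that has little power with so few cohorts. And the term it adds, if common to both arms, cancels from a comparison made within cohorts. At stake are the nominal 5% level of the primary test and the coverage of its confidence interval.

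**Working it through.** **1. The plan's own sample size.** "Considering an effect size of 0.48, a comparison of two groups of 70 subjects would yield 80% power with a two-sided alpha of 0.05". The t-based solution is 69.1, hence 70. With r = 0.5, 70 × (1 − 0.25) = 52.5, hence 53. With 15% drop-out, 53/0.85 = 62.4; 62 is stated, a trivial rounding. Power at 53 per arm is Φ(0.48 / √(0.75 × 2/53) − 1.96) = Φ(2.853 − 1.96) = 0.814. The plan reproduces, with no clustering in it.

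**2. Number and size of clusters.** 124/16 = 7.8 and 124/10 = 12.4, so about 8–12 cohorts, with m = 5–8 trial patients per arm in each. The course size of 8–10 includes non-trial patients and is not the cluster size.

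**3. Closed form.** With n per arm, clustering in one arm and equal total variance σ² in both, the true variance of the difference is (σ²/n)[1 + (m − 1)ICC] + σ²/n. Against the assumed 2σ²/n, the ratio is

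R = 1 + (m − 1) × ICC / 2, and actual alpha = 2[1 − Φ(1.96/√R)].

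| ICC (assumed) | R, m = 5 to 8 | alpha |
|---|---|---|
| 0.01 | 1.020–1.035 | 5.2–5.4% |
| 0.02 | 1.04–1.07 | 5.5–5.8% |
| 0.05 | 1.10–1.175 | 6.2–7.1% |
| 0.10 | 1.20–1.35 | 7.4–9.2% |

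**4. Simulation.** 40,000 null trials per setting on baseline-adjusted residuals, with balanced cells, a group effect in the MBCT arm only, and cohorts/m of 12/5, 9/6 and 8/8. The Monte Carlo standard error is √(0.05 × 0.95/40,000) = 0.11 points. Type I error, range over the three layouts:

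| Analysis | ICC 0.01 | 0.02 | 0.05 | 0.10 |
|---|---|---|---|---|
| No cluster term | 5.2–5.3% | 5.5–6.0% | 6.2–7.0% | 7.3–9.3% |
| Shared cohort term if ICC significant | 5.2–5.4% | 5.5–6.1% | 6.4–7.1% | 7.6–9.5% |
| Shared cohort term always | 5.3–5.5% | 5.7–6.2% | 6.6–7.3% | 7.8–9.7% |
| MBCT-only group term | 4.9–5.0% | 4.9–5.3% | 5.0–5.3% | 5.1–5.3% |

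At ICC 0 every analysis is at about 5%. A repeat simulation of the gated rule gave 6.4–7.3% at ICC 0.05 and 7.5–9.4% at 0.10. The ranges quoted in the conclusion, 6.4–7.3% and 7.5–9.5%, span both runs.

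**5. How often the gate opens.** The cohort ICC test is significant in 8–10% of trials at true ICC 0.05 and 13–17% at 0.10. Tested within the MBCT arm alone, the figures are 14–17% and 26–34%.

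**6. Why a shared intercept does not help.** It enters both arms of a cohort and cancels from the MBCT–CAU difference, so the therapy-group variance is still missing from the standard error. It also takes between-cohort variance out of the residual, which slightly raises the error rate.

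**7. A cohort effect common to both arms** (shared variance 0.05, layout 9/6, no MBCT-group effect). The test with no cluster term gives 4.7% and the gated rule 5.1%, so there is no inflation. An MBCT-only term used alone is conservative here, at 3.7%. The gate opens in 27% of these trials, against 9% in the same layout when the MBCT-group ICC is 0.05 and there is no shared effect. It responds more to the harmless kind of clustering than to the kind that matters.

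**8. Power of a valid test at 53 per arm.** Φ(2.853/√R − 1.96). At ICC 0.05, R = 1.10 gives 0.78 and R = 1.175 gives 0.75. At ICC 0.10 it is 0.69–0.74.

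**The case against.** The strongest objection is that no ICC is given, so the inflation is conditional. A reader might infer that the 5% level fails whether or not the gate opens. The documents do not support that: at ICC 0 the level holds, at 0.01 the excess is at most about 0.4 points, and a cohort effect common to both arms does no harm. Nothing in the protocol points to 0.10 for baseline-adjusted HADS. This stands, and it limits the severity.

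A reader might also take the ICC rule as the stated safeguard of the primary ANCOVA. The text does not settle this, because the sentence follows the secondary mixed model. If it covers only that model, the gate and shared-term arguments do not concern the primary test. The primary test then simply has no cluster term, and its error rate is nearly the same.

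The meaning of COHORT is likewise inferred. The clustering sentence does not say whether the random effect applies to both arms, although the assessment sections favour the two-arm reading. If it meant the MBCT groups only, the term would be suitable but the low-powered gate would remain.

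An analysis plan not shown could improve on this. But the protocol has already written the rule down, and a plan that followed it would inherit the problem.

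**Conclusion.** The concern holds as a conditional one. The protocol does not clearly protect the primary test against therapy-group clustering, and the rule it does give is rarely triggered and, on its natural reading, uses a term that does not account for clustering in the MBCT arm. If the MBCT-group ICC is above 0, the type I error of the gated rule is about 5.2–5.4% at ICC 0.01, 5.5–6.1% at 0.02, 6.4–7.3% at 0.05 and 7.5–9.5% at 0.10.

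These figures rest on an assumed ICC range, balanced cells, 8–12 cohorts, and one MBCT course per cohort with 5–8 trial patients in it. If a cohort's patients were split over several courses, the clusters would be smaller and so would the inflation. The excess is negligible to modest up to ICC 0.05 and material only at 0.10. Severity: should fix, before the analysis.

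**What to change.** - Remove the significance test on the ICC and state that the clustering rule covers the primary analysis.
- Fit the primary model (HADS at T1 on GROUP, HADS at T0, age, gender) with a random effect for the MBCT course attended, in the MBCT arm only, with CAU patients as singletons and Satterthwaite or Kenward–Roger degrees of freedom.
- Include a shared cohort intercept beside it. With balanced cells, the shared effect cancels from each cohort's MBCT–CAU difference, while the therapy-group variance stays in the scatter of those differences. This avoids the conservatism of the MBCT-only term used alone. The combined model was reasoned through, not simulated.
- Carry the same terms into the longitudinal models.
- Record which MBCT course each participant attended; the documents do not say that one cohort equals one course.

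**Cost.** A change of analysis wording and one recorded variable. The variance of the treatment effect rises by about 4–7% at ICC 0.02 and 10–18% at 0.05. The interval therefore widens by about 2–3% (√1.04 to √1.07) and 5–8% (√1.10 to √1.175). Power at 53 per arm should be restated as about 0.75–0.78 at ICC 0.05 instead of 0.81. That is a normal approximation, and the few degrees of freedom from 8–12 courses would lower it a little further. The restatement does not call for enrolling more patients.
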